## Abstract

**Background:**

The incidence of cutaneous malignant melanoma (CMM) is increasing worldwide. In Sweden, over 4600 cases were diagnosed in 2018. The prognosis after radical surgery varies considerably with tumor stage. In recent years, new treatment options have become available for metastatic CMM. Early onset of treatment seems to improve outcome, which suggests that early detection of recurrent disease should be beneficial. Consequently, in several countries imaging is a part of the routine follow-up program after surgery of high risk CMM. However, imaging has drawbacks, including resources required (costs, personnel, equipment) and the radiation exposure. Furthermore, many patients experience anxiety in waiting for the imaging results and investigations of irrelevant findings is another factor that also could cause worry and lead to decreased quality of life. Hence, the impact of imaging in this setting is important to address and no randomized study has previously been conducted. The Swedish national guidelines stipulate follow-up for 3 years by clinical examinations only.

**Methods:**

The TRIM study is a prospective randomized multicenter trial evaluating the potential benefit of imaging and blood tests during follow-up after radical surgery for high-risk CMM, compared to clinical examinations only. Primary endpoint is overall survival (OS) at 5 years. Secondary endpoints are survival from diagnosis of relapse and health-related quality of life (HRQoL). Eligible for inclusion are patients radically operated for CMM stage IIB-C or III with sufficient renal function for iv contrast-enhanced CT and who are expected to be fit for treatment in case of recurrence. The planned number of patients is > 1300. Patients are randomized to clinical examinations for 3 years +/− whole-body imaging with CT or FDG-PET/CT and laboratory tests including S100B protein and LDH. This academic study is supported by the Swedish Melanoma Study Group.

**Discussion:**

This is the first randomized prospective trial on the potential benefit of imaging as a part of the follow-up scheme after radical surgery for high-risk CMM.

**Results:**

The first patient was recruited in June 2017 and as of April 2020, almost 500 patients had been included at 19 centers in Sweden.

**Trial registration:**

ClinicalTrials.gov, NCT 03116412. Registered 17 April 2017, https://clinicaltrials.gov/ct2/show/study/NCT03116412

## Background

The incidence of cutaneous malignant melanoma (CMM) increases rapidly in many countries. In Sweden there was a 35% increase in incidence between 2013 and 2018, from 3400 to 4600 cases [1]. According to the 2016 annual report from the Swedish Cancer Society, the number of cases are expected to multiply during the next decades [2]. Hence, the number of patients requiring follow-up after surgery for CMM will steadily grow in the future.

The reasons for follow-up include:
To early detect and treat locoregional and distant relapses in order to improve survival.To early detect a new primary CMM.To inform, educate and support the patient.

The potential value of follow-up programs after radical surgery for CMM has been a matter of debate for many years, and with little scientific evidence in support. A Dutch trial, randomizing stage IB-IIC patients between conventional and stage-adjusted follow-up by physical examinations in the standard arm according to Dutch guidelines and less frequent physical examinations in the experimental arm. Patient-reported outcome measures (PROMs) were completed at 0, 1 and 3 years after diagnosis. Primary outcome was patients´ well-being and secondary outcomes were recurrences and melanoma-related deaths. One hundred and eighty patients were included and the results were published this year. Analysis three years after diagnosis showed no difference in RFS (recurrence-free survival) or DFS (disease-free survival) [3]. Other studies, published a decade ago, have reported relatively low predictive value of the elevated tumor marker, S100B protein in plasma to detect relapse [4, 5].

An important question is whether imaging should be a part of the follow-up program for patients who have undergone surgery for high-risk CMM. Some studies have investigated the value of follow-up including imaging in this patient group. The MSLT-2 study, in a large number of patients (*n* = 1934), showed in 2017 that repeated controls by ultrasound could replace lymph node dissection in case of a positive sentinel node biopsy (SNB) [6]. However, until now, no randomized study investigating the benefit of whole-body imaging has been conducted. In 2017 the results of an American retrospective study were presented and included 247 CMM patients, 27% followed with clinical examinations only and the remaining 73% underwent a combination of clinical examinations and imaging. The mode of imaging was heterogenous and was limited to chest X-ray for stage IIA/IIB patients. Eighty-seven percent of stage IIC/III patients underwent at least two series of whole body PET/CT or whole body CT plus MRI of the brain. The recurrence rate for stage IIC/III was 23% at a median follow-up time of 31 months. Fifty percent of recurrences in this group were detected by imaging in asymptomatic patients [7].

In a retrospective study of 173 CMM patients from three centers in the UK, CT or FDG-PET/CT plus MRI of the brain were performed according to a UK consensus stipulating repeated imaging up to five years for high-risk patients. Forty-seven per cent had relapsed at a median follow-up time of 23 months, the majority of which (66%) was detected by imaging. Median time to recurrence was ten months. Forty-five per cent of relapsing patients underwent surgery and median OS for this subgroup has not been reached. Median OS for patients who received systemic therapy was 13 months [8]. An Australian study, published in the same year (2018), had a similar approach which but resulted in fewer detected relapses than in the previous study. In a PET database, 170 stage III melanoma patients were identified who regularly had undergone routine FDG-PET/CT +/−MRI of the brain. Melanoma relapse was detected in 38% and mainly (69%) in asymptomatic patients. No relapses were identified by clinical examination without first being reported by patients. Fifty-two percent of relapsing patients underwent surgery. Median follow-up time was 47 months [9].

In addition, a few prospective non-randomized studies have also been conducted. In a Spanish study, published in 2016, almost half of 115 recorded relapses in 290 patients were detected by imaging [10]. In a large German study on patients with all stages of CMM (*n* = 2008), a follow-up program including frequent imaging examinations was prospectively applied. The authors presented the results in 2008 and concluded that the relapses mainly occurred during the first years after radical surgery and earlier in stage III disease compared to stages I-II [11].

The findings in these studies suggest that if a follow-up program is introduced, it should be more intense during or limited to the first years after diagnosis. The observation that more than half of new primary CMMs are detected during the first two years following surgery further indicates that follow-up, if applied, should focus on this time period [11–13]. In a recent Australian cohort study, also with prospective approach, stage III CMM patients (*n* = 154) underwent either CT or FDG-PET/CT at baseline and at least twice annually thereafter. Median follow-up time was 85 months and distant metastasis was identified in 13%. However, 124 out of 1022 examinations were false-positive or showed incidental findings, resulting in unnecessary invasive procedures in 15 patients. The authors concluded in their publication last year that false-positive results and incidental findings occurred in at least half of all patients with substantial additional demands on healthcare resources [14]. This study underlines the costs as a major drawback of intense follow-up programs with imaging. In the choice of imaging, FDG-PET/CT is more expensive than CT, and not as widely available, but covers the whole body and offers slightly better sensitivity than CT. Another difference between the two methods is that a CT scan has a higher predictive value than a PET/CT scan in identifying metastases to the liver and lung. For detection of brain metastases, MRI is better than CT, even though the difference is small when contrast-enhanced high resolution CT protocol is applied as in our study. MRI is associated with long scan times, contraindications (the presence of metal implants) and is more costly and less available than CT [15]. Another negative effect of routine imaging (except for MRI) is the irradiation exposure to the patient, which should not be neglected even though the doses are clearly lower with modern scanners [16].

In recent years, new treatment options have become available for metastatic CMM; immunotherapy and targeted therapy. The introduction of novel drugs emphasizes the need to develop optimal follow-up programs for early detection of recurrent disease, since early onset of treatment seems to improve outcome [17, 18].

According to the Swedish national guidelines [19], blood tests or imaging are not parts of the follow-up schedule for CMM. The current recommendation is clinical examinations only for three years for stage IB-III, except in patients with a positive SNB when lymph node dissection is not performed. These patients for three years regularly undergo ultrasound of the positive regional lymph node region [6]. Despite lack of evidence, there is an international tendency for more frequent imaging, such as in the Nordic countries, except Sweden, where FDG-PET/CT is performed regularly up to five years [20, 21].

In summary, there is lack of evidence regarding the potential benefits of follow-up schedules, and even less so concerning the choice of methods, or schedule intensity to apply. The aim of this paper is to present the study design of the randomized TRIM study, evaluating the effects of adding whole-body imaging and laboratory tests to clinical examinations according to Swedish national guidelines.

## Methods

### Study design

The TRIM study is a prospective randomized multicenter trial in which patients with stage IIB-C or stage III CMM are randomized to follow-up for three years by clinical examination alone according to current Swedish national guidelines +/− whole-body imaging with CT or FDG-PET/CT and laboratory tests including S100B and LDH. All patients are followed with yearly updates of survival for 5 years.

### Endpoints

Primary endpoint is OS at five years.

### Secondary endpoints

The secondary endpoints are survival from diagnosis of relapse and health related quality of life (HRQoL).

### Additional evaluations

Disease-free survival (DFS).The number of imaging examinations in addition to the scheduled.Health economics.The value of blood tests to detect recurrence in comparison to imaging examinations.

### Study population

The study population includes both patients treated for primary melanoma and patients with a recurrent resectable stage III disease. The patients are allowed to receive post-operative adjuvant systemic treatment and / or local radiotherapy according to Swedish national guidelines. In these guidelines it’s recommended that eligible patients are given the opportunity to participate in the study. This helps to achieve adequate participant enrollment. Patients are recruited from all over Sweden at approximately 20 centers, including all university hospitals.

### Key inclusion criteria

Age above 18 years.Signed and dated written informed consent.Radical surgery for stage IIB-C or III CMM.Sufficient renal function for iv contrast-enhanced CT.

### Key exclusion criteria

The patient is assessed as unfit to receive treatment in case of recurrence.Life-expectancy less than 2 years due to concurrent disease.Inability to comply with the follow-up programs.Participation in other clinical trials interfering with the control-program.

### Study procedure and randomization

Written informed consent must be obtained within 8 weeks before randomization. The overall trial design is shown in Fig. 1. The patient must be randomized within 8 weeks after final surgery, i.e. wide excision + sentinel node biopsy or lymph-node dissection.

	1–8 weeks after final surgery(a)			Visit applicable for stage III patients only	Letter contact		Visit applicable for stage III patients only			
Informed consent (within 8 weeks prior to randomization) (b)	X									
Inclusion/exclusion criteria	X									
Demographics	X									
Cancer/treatment history (c)	X									
Physical examination (d)	X	X	X	X (d)		X	X (d)	X		
Biochemistry (e)	X	X	X			X		X		
CT scan thorax/abdomen/brain or iv contrast enhanced whole-body FDG-PET/CT including brain (f)	X (i)	X	X			X		X		
Ultrasound of affected lymph node location (g)				X (g)			X (g)			
HRQoL (h)	X		X		X	X		X		

^a^An imaging examination carried out before but within two months of randomization is adequate as baseline assessment for both groups under the prerequisite that the same method is used for future examinations. Final surgery is defined as wide excision and/or sentinel node biopsy or lymph-node dissection.

^b^Written informed consent must be obtained before any study-specific screening procedures are performed.

^c^Includes thickness of primary tumour, number of examined nodes/nodes with metastases, TNM staging, postoperative treatment (i.e. adjuvant radiotherapy, adjuvant systemic treatment).

^d^To be performed according to clinical routines. Months 18 and 30: Visit applicable for stage III patients only. FU year 4 and 5 is for overall survival only. If visit at the clinic is not planned, a review of medical records is sufficient.

^e^Biochemistry: s-creatinine, S-S100B, ALP, LDH, AST and/or ALT.

^f^The mode of imaging (CT scan of the lungs, abdomen and brain or i.v. contrast enhanced whole body FDG-PET-CT including brain) is chosen by the investigator at baseline and the same mode is used for the subsequent examinations.

^g^To be done shortly before the scheduled visits, that are not preceded with whole body imaging examination, for stage III patients who have not had lymph node dissection.

^h^HRQoL (EORTC QLQ-C30 and HAD) will be carried out at sites with an oncologist as PI. The assessments will be performed at the study center, just before the study visits, preferably on a web-based device (if not available, paper formula is accepted). At 21 months the HRQoL will be completed remotely between on-site visits.

^i^If not performed within 8 weeks before randomization, it should be done within 28 days post-randomization at the latest.

### Extra visits and investigations

Extra diagnostic evaluation such as imaging and laboratory tests are allowed for all subjects presenting signs and/or symptoms. Patients in both groups are instructed to contact their study center if they experience any symptoms suspicious of recurrence. Additional controls are registered in the eCRF under “Extra visits”.

### Health related quality of life (HRQoL)

For logistical reasons, HRQoL assessments are only carried out at sites with an oncologist as principal investigator (PI). The assessments are scheduled at baseline and at visits at 12, 24 and 36 months. The baseline assessment is performed after the informed consent procedure but before randomization. Thus, the patient should be unaware of the result of randomization when completing the first HRQoL-questionnaire. The assessments are made at the study center, just before the study visits, preferably on a web-based device administered by a research nurse. Validated HRQoL-instruments are used (EORTC QLQ-30 and HAD-scale). Additionally, at month 21, a letter is sent to the patients asking them to complete an extra HRQoL questionnaire at home, including a prepaid return envelope.

### Questionnaires

The EORTC Quality of Life Core Questionnaire (EORTC QLQ-C30), Version 3 is a cancer-specific questionnaire consisting of 30 items including five functional scales (physical-, role-, emotional-, cognitive-, and social functioning), three multi-item symptom scales (fatigue, pain, nausea and vomiting), five single items (dyspnea, loss of appetite, constipation, insomnia, diarrhea, financial difficulties related to the disease) and a global quality of life scale [22]. The responses are scored with 4-point scales ranging from 1 (“Not at all) to 4 (“Very much”), with the exception of the two items assessing global quality of life which are scored on a 7-point scale ranging from 1 (“Very poor”) to 7 (“Excellent”). The time frame is “during the previous week”. Reference values from the Swedish population are available [23].

The Hospital Anxiety and Depression Scale (HAD-scale) is developed to assess anxiety and depressive symptoms in somatically ill patients [24]. It consists of 14 items, 7 assessing anxiety (HAD- A) and 7 assessing depression (HAD-D). The presence of problems during the preceding week is rated on a four- graded scale from 0 (“No problem”) to 3. The scores for each subscale are summed, giving a maximum of 21. Two cut-off points have been suggested: 0–7 no problems of clinical relevance (non-cases), 8–10 cases that warrant further psychiatric investigation (possible cases), and ≥ 11 clinical levels of anxiety/depression (probable cases). The HAD-scale has been widely used and the Swedish version has been validated in patients with CMM [25] and in breast cancer patients [26].

### Duration

Follow-up according to protocol will continue for three years if no signs of recurrent disease. In case of loco-regional recurrent disease treated with radical surgery, the patient restarts the follow-up program in the same study arm if all inclusion criteria for the study still are met. All patients will be followed for survival for 5 years with survival updates at 4 and 5 years.

Discontinuation criteria
Withdrawal of consent.Inappropriate enrollment.Recurrent stage IV or unresectable stage III CMM.Subject unable or unwilling to continue follow-up program according to protocol.Conditions leading to frequent radiological assessments other than stipulated by the TRIM study protocol, for example enrollment in other clinical studies or other malignancies.

### Statistical considerations

The sample size is based on the primary endpoint OS at 5 years.

Based on data from the Swedish Melanoma Registry, the following numbers of patients diagnosed and classified according to AJCC7 (version 7) are expected:
Stage IIB-C: 325 patients/year with a risk of recurrence during the first 3 years of 20–30%.Stage III: 350 patients/year with a risk of recurrence during the first 3 years of 50–60%.

The 5-year mortality for the entire group is estimated at 40% and we aim to detect a difference in hazard ratio for death of at least 20%. With a risk of type 1 error of 5% and type 2 error of 15%, 573 patients should be randomized to each group. With an expected dropout rate of about 10%, the planned number of randomized patients should be 1300.

However, with the introduction of systemic adjuvant treatment for stage IIIB-D patients in early 2019, less relapses are expected to occur in this subgroup. Impressive long time results for systemic treatments in advanced disease have also been presented [27, 28]. Hence, more patients than originally planned need to be included to meet the statistical requirements. Therefore, updated power calculations taking these factors into consideration are planned when final OS results for the pivotal adjuvant studies (COMBI-AD, CheckMate 238 and KEYNOTE-054) have been compiled (www.clinicaltrials.gov; NCT01682083, NCT02388906 and NCT02362594). Since the final OS analysis for the COMBI-AD study is planned in the end of 2021, the final OS results of CheckMate 238 will most likely also be presented next year and the final OS analysis for the Keynote-54 study is expected in less than three years, we plan to conduct new power calculations in autumn 2023. We expect that patient recruitment has not ended by then.

Results will be evaluated both on an intention-to-treat basis and per protocol. Patients who withdraw their informed consent remain in their allocation group when evaluated on the intention-to-treat basis, and are excluded when evaluated on the fulfilled protocol basis.

Survival data will be analyzed according to the Kaplan-Meier method and comparison between groups will be performed with the log-rank method. Binominal data will be analyzed with Chi-square statistics and continuous data with Mann-Whitney U test. Level of significance two-sided *p* < 0.05.

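### The 573 patients per group do not follow from the stated inputs: for a hazard ratio of 0.80 they give about 63–67% power, not 85%

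*Protocol article*

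**What the plan says.** All the inputs are in the Protocol article.

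- Basis: "The sample size is based on the primary endpoint OS at 5 years" (Statistical considerations).
- Event rate: "The 5-year mortality for the entire group is estimated at 40" per cent. The text does not say whether this is the rate under standard follow-up or the average over both arms.
- Effect: "we aim to detect a difference in hazard ratio for death of at least 20" per cent.
- Errors and result: "With a risk of type 1 error of 5% and type 2 error of 15%, 573 patients should be randomized to each group". About 10% dropout then raises the total to 1300.
- Analysis: log-rank comparison, with "Level of significance two-sided" p < 0.05.
- Follow-up: "All patients are followed with yearly updates of survival for 5 years" (Study design). The Duration section says the same.
- Allocation: 1:1 (Study procedure and randomization).

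The same section adds that more patients than planned will be needed, because of adjuvant treatment and better systemic therapy, and schedules new power calculations for autumn 2023.

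**The concern.** The power of a log-rank test depends on the number of deaths. At 40% five-year mortality, 1146 patients followed for five years produce somewhat more than 400 deaths. That is well short of what a hazard ratio of 0.80 requires at 85% power, so the published inputs and the published result disagree.

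The Discussion contrasts intensive imaging programmes with a minimal practice that may do as well, and expects the results to shape guidelines. A non-significant result from a trial believed to have 85% power for a 20% reduction in hazard would be read as stronger evidence against imaging than it is. The gap exists at the original 40% mortality, before any fall in event rates from newer treatments.

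**Working it through.** **Inputs.** Hazard ratio (HR) 0.80; two-sided alpha 5% (z = 1.960); power 85% (z = 1.036); 1:1 allocation; five-year mortality 40%; five years of follow-up per patient; 573 × 2 = 1146 patients. Proportional hazards are assumed.

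**1. Deaths needed (Schoenfeld).**
D = 4 × (1.960 + 1.036)² / (ln 0.80)² = 4 × 8.978 / 0.0498 = 721.3, so 722. Freedman's formula gives 728.

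**2. Deaths expected from 1146 patients.**
- 40% as the control rate: experimental mortality is 1 − 0.60^0.80 = 33.5%, the mean is 36.8%, and 1146 × 0.3677 = 421 deaths.
- 40% as the rate over both arms: 1146 × 0.40 = 458 deaths.

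To reach 722 deaths, mortality would have to be 722 / 1146 = 63%.

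**3. Attempt to reproduce 573 per group.**
- Control rate 40%: 722 / 0.3677 = 1963 patients, about 982 per group.
- Pooled rate 40%: 722 / 0.40 = 1805 patients, about 903 per group.

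Neither is near 573.

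**4. Power for HR 0.80.** Power = Φ(√D / 2 × 0.2231 − 1.960).

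| Patients contributing | 40% is | Deaths | Power |
|---|---|---|---|
| 1146 | control rate | 421 | 63% |
| 1146 | pooled rate | 458 | 67% |
| 1300 | control rate | 478 | 68% |
| 1300 | pooled rate | 520 | 72% |

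A one-sided 5% test, which the plan does not specify, would give 74–77% with 1146 patients.

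**5. Effect detectable with 85% power at 1146 patients.** HR = exp(−2 × 2.996 / √D).
- Pooled 40%, 458 deaths: 0.756.
- Control 40%, 410 deaths at the solution: 0.744.

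So about 0.75.

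**6. Could the 20% be a relative fall in five-year mortality?**
- 40% versus 32% (HR ln 0.68 / ln 0.60 = 0.755): 631 per group by log-rank, about 645 by two proportions. With 573 per group the power is 81%.
- Risk ratio 0.80 around a pooled 40%, that is 44.4% versus 35.6% (HR about 0.75): 531 per group by log-rank, about 545 by two proportions, about 567 with continuity correction.

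The second version comes close to 573 at two-sided 5% and 85% power, though it does not give it exactly.

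**7. Dropout step.** 1146 / 0.9 = 1274, rounded up to 1300. This step is sound.

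**The case against.** The strongest defence is that the patient number is right and only the label is wrong. The section sizes the trial on survival at five years and gives mortality for the whole group, so a 20% relative reduction in five-year mortality around a pooled 40% is a plausible intention. On that reading 573 per group is enough, with about 87% power without continuity correction. This stands as a possible explanation, and it means the document does not show that the trial is too small for the effect its designers had in mind. It does not rescue the text, which says hazard ratio. That reading corresponds to a hazard ratio of about 0.75.

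A second defence is that the plan already expects to enrol more and to recalculate in 2023, so 1300 is not final. That is true, but the reasons given are adjuvant and systemic therapy, not this mismatch. Nor do the documents say that the recalculation will reuse the old figures, so a carried-over error is a risk and not an established fact.

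Three stronger inferences should be resisted:

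- **A true 20% reduction would be missed more than one time in three.** The miss rate is 33–37% with 1146 patients, but 28–32% if all 1300 contribute. The latter is realistic, because patients who withdraw consent stay in their group for the intention-to-treat analysis and record review suffices for survival in years 4 and 5.
- **573 is really a number of deaths.** A one-sided 5% calculation for HR 0.80 gives 577.5 deaths, which is not 573, and the plan states a two-sided level.
- **Survival follow-up must be lengthened.** Nothing in the arithmetic requires it; that would be a change of design.

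**Conclusion.** The point holds as an inconsistency between the stated effect and the stated number. For HR 0.80 at two-sided 5%, power is 63–67% with 1146 patients and 68–72% with 1300, against the 85% stated. Keeping 85% power for that effect would take roughly 900–980 per group in place of 573. The width of each range comes from whether 40% is the pooled or the control rate. The figures assume proportional hazards and survival follow-up ending at five years, as the plan states.

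The conclusion stops there. Whether the effect measure or the sample size is the mistaken element cannot be settled from the document. A mislabelled relative reduction in five-year mortality is the closest explanation found, but it remains an inference.

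**What to change.** Reconcile the effect wording with the number under Statistical considerations.

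1. Restate the calculation, for example: 1146 evaluable patients give about 420–460 deaths, 63–67% power for a hazard ratio of 0.80, and 85% power for a hazard ratio of about 0.75. State the number of deaths explicitly.
2. Say whether 40% is the control or the pooled rate, and whether the 20% refers to the hazard or to five-year mortality.
3. Start the planned 2023 recalculation from these figures before adjusting for newer treatments.

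The cost is wording only, and the stated power becomes less favourable. If the sponsor wants to keep 85% power for HR 0.80, that is no longer a wording change: about 1806–1964 evaluable patients are needed, or about 2010–2180 with 10% dropout.

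Following vital status to a common cut-off, beyond each patient's five years, is at most an optional design choice. Under constant hazards it would reach about 78–84% power. It would also alter the stated endpoint and follow-up, and could dilute an effect that fades once imaging ends at year 3. It is not part of this correction.
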